#### Other study parameters

The economic aspect will be published based upon an estimation of the direct medical healthcare costs for TTT + PT and conservative care for PFP + PT, including costs for hospital visits, scans, surgery, physiotherapy, prescription medication, and possible readmission. The medical costs are based on resource costs. Furthermore, ROH and complications will be reported.

#### Methods for additional analyses (e.g., subgroup analyses)

Per-protocol analyses will be performed including only the patients that did not crossover from the PT to TTT group, for comparison with intention-to treat analysis.

Methods in analysis to handle protocol non-adherence and any statistical methods to handle missing data.

Patient adherence to the PT will be extracted from the weekly questionnaire and will be reported. To test whether this affects the primary outcome, adherence will be added as extra covariate in the multivariable linear regression analysis as sub analysis.

In the case of missing outcome values, data will be imputed before analysis using multiple imputation methods.

Plans to provide access to the full protocol, participant-level data and statistical code.

The trial protocol provided to the METC is available from the corresponding author upon reasonable request. Data will be handled according to the FAIR principles (a guideline to improve the Findability, Accessibility, Interoperability, and Reusability of Digital Assets) [37]. After completion of the study, metadata will be available upon request. For access to anonymised participant-level data and statistical code, an application can be submitted to the corresponding author.

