#### TTT and PT versus PT only

The study involves four outpatient visits (at inclusion/randomisation, 6 weeks after the start of the intervention, after 12 (PT group)/18 weeks (surgery + PT group), and after 26 weeks in both groups). A physical examination will take place at every outpatient visit, with the addition of the decline step-down test (DSDT) at baseline and 12/18 weeks after randomisation. Patients will complete online questionnaires at every outpatient visit and 12 months after randomisation.

After randomisation, patients will either have a TTT (treatment group) or start with the PT (control group). From 12 weeks, there will be the possibility to crossover from the PT group to surgery if the symptoms do not improve. The criteria for this are a persisting high level of pain and patient-reported lack of effect of the PT. In that case, surgery will be performed within 2 weeks. Participants will then follow the same protocol as the TTT group, including the PT programme, surveys, and physical measurements.

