### Outcomes

#### Primary outcome

The main study parameter will be the between-group difference in activity-related knee pain at 12 weeks after PT in both groups, measured with the 10 cm VAS-scale. The point in time is different for the two groups, since there is a 6 week splint phase incorporated in the TTT group. Thus, knee pain will assessed at week 18 in the TTT group (6 weeks for the TTT and splint + 12 weeks of PT) and at week 12 in PT group. To compare both treatments as reliably as possible, we opted to not set this outcome measure further in time, due to the possibility for cross-over from the PT group to the TTT group. Furthermore, we expect that a plateau phase of pain will be reached within this period. The mean from the two VAS pain scores in week 12 (PT group) and 18 (TTT group) by the weekly questionnaire and outpatient visit will be used to account for variance in pain levels. Participants will assess the maximum pain they had felt during the previous 7 days when participating in activities of daily living such as ascending stairs, descending stairs and standing up from a sitting position. The 10-cm VAS is a valid and responsive tool for evaluating overall pain in patients with PFP [28]. A minimal clinically important difference (MCID) of 2 cm or 20% has been reported to reflect real changes in a patient’s symptoms [28].

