### Sample size

Our primary outcome is the between-group difference in overall knee pain 12 weeks after PT and 18 weeks after TTT and PT, measured with the VAS score. Our hypothesis is that the improvement in the TTT group will be greater than the improvement in the PT group.

To detect the superiority of the treat-to-target TTT with PT to PT alone, we calculated the required sample size for an independent samples t-test on the following assumptions: power (1-beta) 0.8, significance level (alpha) 0.05, and two-sided testing. Effect size was set at the MCID for VAS-pain, based on a study by Crossley et al., who demonstrated that a change in the VAS score of two points or more is considered clinically relevant and worthwhile for performing surgery [28]. Based on a study by Bayoumi et al., which compared different surgical techniques for patellar maltracking without instability, the anticipated mean for the PT only group was 6.2 (reflecting the pre-operative value), and SD was 2.0 [17]. Based on these parameters, a sample size of 16 patients per group is needed. Anticipating on a loss to follow-up of 20%, 20 patients per group are needed.

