### Statistical methods for primary and secondary outcomes

In accordance with the iPFRN, the REPORT-PFP consensus statement outcome measure description will be adequate [35]. The items described in the assessment will be in adequate detail to allow replication. We will report *n* (%), the mean (SD), and median (interquartile range; IQR) for categorical/descriptive, normally distributed continuous and non-normally distributed continuous data, respectively [35]. Results over time will be visualized descriptively in spaghetti plots. The primary analyses will be performed following the intention-to-treat method.

Statistical analyses will be done using *R* software (R Foundation for Statistical Computing, Vienna, Austria).

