#### Primary endpoint

The primary outcome parameter is the between-group difference in VAS score, at 12 weeks after start of the PT (week 18 for TTT group). For analysis of the primary parameter, the mean of the two VAS scores at 12 weeks of the PT in the TTT group will be compared with that of the PT group. Baseline VAS score, biological sex, and treatment group will be included as covariates in a multivariable linear regression analysis.

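### The per-protocol set removes only physiotherapy patients who crossed over, who do so because pain persisted, so this additional comparison is biased toward physiotherapy

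*Protocol article*

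**What the plan says.** The section on additional analyses defines the per-protocol set by a single condition: "Per-protocol analyses will be performed including only the patients that did not crossover from the PT to TTT group". The result is to be set beside the ITT result. The sentence names no endpoint or visit.

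The section comparing the two treatment strategies gives the crossover rule: "From 12 weeks, there will be the possibility to crossover from the PT group to surgery if the symptoms do not improve". It adds: "The criteria for this are a persisting high level of pain and patient-reported lack of effect of the PT". Crossover runs in one direction only, from PT to surgery.

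Under Primary outcome, pain is read at week 12 in the PT arm and week 18 in the TTT arm. The authors explain the timing: "we opted to not set this outcome measure further in time, due to the possibility for cross-over from the PT group to the TTT group".

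Under the statistical methods, "The primary analyses will be performed following the intention-to-treat method". The primary model is fixed as well: "Baseline VAS score, biological sex, and treatment group will be included as covariates in a multivariable linear regression analysis". The Discussion accepts that crossover can affect comparisons beyond 12 weeks and relies on ITT to contain this. It does not mention selection in the per-protocol set.

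**The concern.** The reason for exclusion is a poor result on, or very close to, the outcome being compared. Taking those patients out of the PT arm leaves a PT group that did better than the group randomised. The stated exclusion takes out no TTT patient whose pain persisted.

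At 12/18 weeks the exclusion also repairs nothing. Crossover opens only from week 12, so a crossover patient's week-12 score was obtained under PT alone and is a valid PT outcome.

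At 26 weeks and 12 months there is a real problem to address, because the ITT comparison then includes PT-arm patients who have had surgery. The only alternative named exchanges that contamination for selection.

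What is at stake is interpretation. Because the two results are meant to be compared, ITT and per-protocol could differ through selection alone. A reader could then take the smaller per-protocol figure for the effect without crossover.

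**Working it through.** **Inputs from the Sample size section.** SD 2.0 cm; target difference 2 cm; "power (1-beta) 0.8, significance level (alpha) 0.05, and two-sided testing"; 20 per arm after allowing for 20% loss.

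**The plan's own figure.** n per arm = 2 × (1.960 + 0.842)² × 2.0² / 2² = 15.7, so 16. Then 16 / 0.8 = 20. Both figures reproduce, so SD 2.0 and a 2 cm difference are used below.

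**Assumptions not in the article.** Crossover share f = 30% of the PT arm; correlation ρ = 0.7 between the tendency to cross over and week-12 pain; correlation r = 0.5 to 0.7 between baseline and endpoint VAS; all 20 per arm analysed.

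**Step 1: selection exactly by pain, no covariates.** If the worst fraction f of PT patients leaves, the PT mean falls by SD × φ(z) / (1 − f), with z the upper-f normal cut-off.
- f = 20%: 2 × 0.280 / 0.8 = 0.70 cm
- f = 30%: 2 × 0.348 / 0.7 = 0.99 cm
- f = 40%: 2 × 0.386 / 0.6 = 1.29 cm

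**Step 2: imperfect selection.** Multiply by ρ. At f = 30%: 0.7 × 0.99 = 0.70 cm. Simulation with 20 per arm gives 0.65 to 0.66 cm and about 17% rejection under no true difference. With a true 2 cm benefit, power falls from 87% (ITT) to 50%. These figures are without covariates, which is not the planned model.

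**Step 3: the planned adjustment for baseline VAS.** Selection also shifts the baseline mean of the retained PT patients, and the regression removes that part. Approximately, remaining bias = unadjusted bias × (1 − r²).
- r = 0.5: 0.70 × 0.75 = 0.52 cm
- r = 0.7: 0.70 × 0.51 = 0.36 cm

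Simulation with baseline VAS in the model (sex omitted) agrees:

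| | r = 0.5 | r = 0.7 |
|---|---|---|
| Spurious PT advantage, no true difference | about 0.5 cm | about 0.35 cm |
| Rejection at nominal 5% | 13% | about 11% |
| Apparent benefit when the truth is 2 cm | about 1.5 cm | about 1.65 cm |
| Power, ITT to per-protocol | 94% to 68% | 99% to 90% |

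Part of the power loss comes simply from having about 0.30 × 20 = 6 fewer PT patients; it is not all bias.

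**Step 4: sensitivity.** A separate simulation used baseline VAS and sex as covariates, r = 0.5 and f from 20% to 50%. With no true difference, the spurious PT advantage is 0.28 to 0.60 cm at ρ = 0.5 (7 to 12% rejection). At ρ = 1 it is 0.54 to 1.26 cm (14 to 46% rejection). At ρ = 0 there is no bias. Every scenario with ρ above zero shifts toward PT.

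**The case against.** The strongest defence is that this is a secondary analysis presented beside ITT. No trial conclusion is attached to it, and its bias runs against the trial's own hypothesis, so it cannot create a false claim for surgery. That stands, and it limits the severity.

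The analysis may also be meant only for follow-up beyond 12 weeks, where ITT is contaminated by crossover surgery. The text is compatible with that reading, since it names no visit, and the Discussion confines its worry to later comparisons. This answers the 12/18-week part only if the plan says so. It does not remove the selection at later visits.

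Four stronger readings are tempting, and the article does not support them.
- A reader might infer that the primary result is biased. It is not, because the primary analysis is ITT.
- A reader might infer that TTT patients who were never operated on stay in the per-protocol set. That rests on the silence of one sentence in a condensed article; the full definition may stand elsewhere.
- A reader might take 0.66 cm and 50% power as the size of the problem. Those figures hold only without the planned covariates.
- A reader might infer from the PT mean of 6.2, taken from pre-operative values, that crossover will be common. That is a sample-size assumption, and the article gives no crossover share.

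**Conclusion.** The concern holds for the additional per-protocol analysis. As written, the rule selects PT responders and biases that comparison toward PT, so it understates any benefit of TTT. At 12/18 weeks the exclusion has no corrective purpose.

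Under the planned adjustment for baseline VAS and the assumptions stated, the bias is about 0.35 to 0.5 cm against a 2 cm target, roughly 18 to 25% of it. The size moves with the crossover share and with how closely crossover follows pain. It vanishes only if crossover is unrelated to pain, which the crossover criteria make implausible. The calculations model the 12/18-week comparison; no figure is available for 26 weeks or 12 months, where the same selection operates.

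This should be fixed, but it does not threaten the primary conclusion.

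**What to change.** 1. State which visits the per-protocol analysis covers, and that no crossover-based exclusion applies at 12/18 weeks: all randomised patients are kept, because PT-arm values there precede crossover surgery.
2. For 26 weeks and 12 months, add or substitute an analysis that keeps all randomised patients, treats PT-arm values after crossover as missing, and uses baseline, weekly and week-12 VAS in the mixed model or the multiple imputation. These scores are already collected and drive crossover. State the missing-at-random assumption. This is one option among several; inverse-probability-of-censoring weighting is another.
3. If the naive per-protocol result is still reported, label it as biased toward PT.

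The cost is wording and modest programming, with no new data or patients. The downside is reliance on missing at random, and wider intervals if many cross over.

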#### Physiotherapy (PT) programme

This will start as soon as possible in the PT group and after the splint phase in the TTT group; the PT group will not wear a splint. The PT will consist of three levels and will be supervised by a physiotherapist. According to predefined criteria, the physiotherapist decides whether a patient can step onto the next level within the PT. The PT consists of flexibility, neuromuscular coordination, and strength exercises for the quadriceps and hip muscles. The PT is developed by a team of experienced physiotherapists who are specialised in treating patients with PFP and based upon the most recent physiotherapeutic insights [8]. In addition to training, education about PFP is incorporated into the PT according to the most recent insights regarding pain mechanisms [26, 27]. Physiotherapists who participate as self-chosen treating health care professionals by patients will be requested to follow an instructional video developed by the REVITALISE study team. Additionally, the three levels of exercise of the PT programme are available on the Physitrack^®^ tool for both participating physiotherapists and patients with PFP to improve exercise adherence and support clinical decision-making. In total, there will be 12 sessions with the physiotherapist. In the first three weeks of the PT, patients visit the physiotherapist twice a week. This will occur once a week from week 3 to week 6. This will occur every other week from week 6 to week 12. However, the treating physiotherapist may increase or decrease the number of appointments if needed. Additionally, the physiotherapist may adjust the exercises, sets, repetitions, weight and duration of loading tailoring to the specific needs of the patient. Since it is our intention that the PT is adjusted to the needs of each individual patient, the exact adherence and deviations to the protocol will not be monitored specifically. However, if necessary, we will consult with the treating physiotherapist in case the patient is not compliant. Moreover, the physiotherapist will be contacted by the study coordinator at the end of the PT to inquire about possible feedback on the PT and patient adherence and progression. The PT is included in the supplementary material (Supplementary file 1), which contains more detailed information and instructions.

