#### Strategies to improve adherence to interventions

To improve adherence, patients will receive the PT in text and with visual instructions on the Physitrack app if possible. They will also receive a weekly questionnaire to register the amount of exercising with the physiotherapist and at home, as well as their VAS score during the 12-week PT.

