#### Other study parameters

This study will include items strongly recommended by the International Patellofemoral Research Network (iPFRN) in the REPORT-PFP consensus statement [35]. These include demographics, such as age, biological sex, symptom duration, and unilateral/bilateral symptoms [35]. Furthermore, physical examination data, such as height and weight (and hence BMI) will be recorded. To evaluate the adherence to the PT, patients will also receive a weekly email during the PT asking how often they have visited the physiotherapist and how often they have executed the PT at home.

Any adverse events (AEs) will be monitored, as explained in the ‘Adverse event reporting and harms’ section. The rate of ROH after surgery will be registered as a separate outcome.

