## Discussion

The REVITALISE study is the first RCT to compare surgical intervention followed by PT to PT alone in patients with chronic PFP. This study’s results will gain insight into the most effective treatment for patients with chronic PFP and will enhance our treatment of this high burden disease with currently a high variability of provided care [14]. This variation seems to be not or weakly associated with patient characteristics, elucidating the need for a more standardised approach to prevent over- or under treatment. The study will answer the question whether patients receiving TTT followed by PT have less pain and better functional outcomes than those receiving PT alone. In addition to measuring the effectiveness of TTT plus PT versus PT alone, a range of other outcomes will be assessed (e.g., physical function, complications, direct medical costs), to provide a broader view of the effect of both treatments.

The strengths of the study include the randomised controlled design supported with multiple involved professions. Physiotherapists are involved in the design of the PT. Orthopaedic surgeons are involved in the TTT protocol. Since this is a single-centre study, little or no variation in surgical technique is expected.

This study has several limitations. First, the crossover design potentially affects long-term (i.e., > 12 weeks) comparisons of the groups, as well as induces bias in cases where patients become less motivated to follow physiotherapy. However, as the primary analysis is according to the intention-to-treat principles, we do not expect this to have a major impact. Second, at the time of presentation at the hospitals, patients will have had different treatments, i.e., the care given by the family physician, the outpatient physiotherapist, or other involved professionals. In our physiotherapy programme, special care is given to education of the patient about PFP, as well as a focus on building balance and strength in multiple muscle groups, not only the quadriceps. Third, for logistical reasons, it is not possible for all participants to receive physiotherapy from the same physiotherapist. To limit protocol variations, we will contact each physiotherapist to explain the research design, the PT, and the need to adhere to this programme. Simultaneously, the physiotherapist should tailor the programme to the participants, as their individual needs and limitations are always the highest priority.

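### Adding physiotherapy adherence to the primary regression cannot show whether adherence affects pain, and the treatment coefficient in that sub-analysis loses the protection of randomisation

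*Protocol article*

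**What the plan says.** The primary model in the section Primary endpoint holds only baseline variables and arm: "Baseline VAS score, biological sex, and treatment group will be included as covariates in a multivariable linear regression analysis". The primary analysis is by intention to treat.

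Under Methods for additional analyses, adherence is taken from the weekly questionnaire and entered as a further term, with the purpose stated: "To test whether this affects the primary outcome, adherence will be added as extra covariate in the multivariable linear regression analysis as sub analysis".

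Adherence is self-reported during the programme. According to Other study parameters, "patients will also receive a weekly email during the PT asking how often they have visited the physiotherapist", and the e-mail also asks how often the exercises were done at home. Strategies to improve adherence shows that the same weekly questionnaire records exercise "as well as their VAS score during the 12-week PT".

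Three further statements bear on what adherence depends on:
- Physiotherapy (PT) programme lets the treating physiotherapist change the number of appointments and the exercises according to need.
- TTT and PT versus PT only offers crossover to surgery from week 12 to the PT group alone, on persisting high pain and reported lack of effect.
- The Discussion says that the crossover option "induces bias in cases where patients become less motivated to follow physiotherapy".

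**The concern.** Adherence is a post-randomisation variable. In the TTT group it is measured after surgery and the splint phase. It is recorded alongside pain, and the final weekly VAS is one of the two scores averaged into the primary outcome.

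The stated question is causal: does adherence affect the outcome? A regression coefficient answers it only if nothing that influences adherence also influences pain, and if pain does not influence adherence. The protocol's own text makes both unlikely, because appointments vary with need and motivation may depend on how the patient is doing.

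The same model also yields a treatment coefficient. If arm shifts adherence, directly or through pain, that coefficient no longer compares the groups as randomised. Printed beside the primary result, it could be taken for the effect of surgery with adherence accounted for.

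**Working it through.** **Inputs from the Protocol article (Sample size).** Difference 2 cm, SD 2.0, two-sided alpha 0.05, power 0.80, loss 20%. The stated sizes reproduce with the normal approximation: 2 × (1.960 + 0.842)² × 2.0²/2² = 15.7, so 16 per group; 16/0.80 = 20. This point changes neither figure. The SD and the 2 cm effect are carried into the checks below.

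**Assumed inputs.** The documents give no value for how arm, prognosis or pain relates to adherence. All such links below are assumptions.

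**Check 1: prognosis influences both adherence and pain.** Let A = 1 for TTT, U = unmeasured prognosis (SD 1), M = adherence and Y = VAS.
- M = aA + bU + error, within-arm SD 1
- Y = δA + gM + cU + error, within-arm SD 2.0
- Total treatment effect τ = δ + ga, set to -2.0; c = 1.0

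Regressing Y on A and M gives
- adherence coefficient = g + cb (truth: g)
- treatment coefficient = τ - a(g + cb)

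| a (SD) | b | g | Treatment: formula | Treatment: simulated | Adherence: simulated (truth) |
|---|---|---|---|---|---|
| 0 | -0.5 | 0 | -2.00 | -2.00 | -0.50 (0) |
| 0.5 | 0 | 0 | -2.00 | -2.00 | 0.00 (0) |
| 0.5 | -0.3 | 0 | -1.85 | -1.84 | -0.30 (0) |
| 0.5 | -0.5 | 0 | -1.75 | -1.75 | -0.50 (0) |
| 1.0 | -0.5 | 0 | -1.50 | -1.50 | -0.50 (0) |
| -0.5 | -0.5 | 0 | -2.25 | -2.26 | -0.50 (0) |
| 0.5 | -0.5 | -0.5 | -1.50 | -1.51 | -1.00 (-0.5) |

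The simulations used 1,000,000 patients each. Without adherence, the model returned -1.99 to -2.01 throughout. In the last row the direct effect is -2.0 - (-0.5 × 0.5) = -1.75, so -1.51 is neither the total nor the direct effect.

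**Check 2: final pain itself drives adherence.** M = dA + sY + error (SD 1), with no effect of adherence on pain. With an assumed baseline correlation of 0.4, the residual variance of Y is v = 4 × (1 - 0.16) = 3.36. Then
- adherence coefficient k = sv/(s²v + 1)
- treatment coefficient = τ - k(d + sτ)

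For s = -0.4 sessions/week per cm: k = -1.344/1.5376 = -0.87.
- d = 0: -2 + 0.874 × 0.8 = -1.30
- d = 0.5: -2 + 0.874 × 1.3 = -0.86
- d = 1: -2 + 0.874 × 1.8 = -0.43
- d = -0.8: d + sτ = 0, so -2.00; the two sources cancel

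For s = -0.2: k = -0.672/1.1344 = -0.59. With d = 0, treatment is -2 + 0.592 × 0.4 = -1.76.

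With no true treatment effect and d = 0.5, treatment is -kd: +0.30 (s = -0.2) to +0.44 (s = -0.4), favouring PT. If s has the opposite sign, so that more pain means more sessions, the same sum gives -0.30 to -0.44, favouring TTT.

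Simulating 4,000 trials of 20 per arm agreed with these values. The adherence term was significant at 5% in about 57% (s = -0.2) to 98% (s = -0.4) of trials, although adherence had no effect.

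**Reading the two checks together.** The adherence coefficient is wrong whenever prognosis or pain is linked to adherence. The treatment coefficient needs something more: an arm effect on adherence as well, or pain driving adherence.

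**The case against.** The strongest defence is that this is labelled a sub-analysis, that its declared purpose concerns adherence and not the treatment effect, and that the primary estimate contains no post-randomisation term. All of that stands. Nothing in the article says that an adherence-adjusted treatment effect will support conclusions.

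A reader might go further than the documents allow in three ways.

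- **Both coefficients are always biased.** Not so. In the first row of Check 1 the treatment coefficient is -2.00. The Discussion makes an arm effect on adherence plausible but gives no size.
- **The bias shrinks the benefit of surgery, perhaps to 0.4 cm.** This needs Check 2 at its extreme. There, adherence follows from pain in the last 7 days, although most adherence precedes that week. Twelve planned sessions in 12 weeks average one per week, so a difference of one supervised session per week would equal the whole supervised programme; only home exercise could supply it. A slope of -0.4 implies a residual correlation of -0.4 × √3.36/√1.5376 = -0.59. The sign is open too, because appointments may be raised or lowered with need.
- **The plan contradicts itself by saying that "the exact adherence and deviations to the protocol will not be monitored specifically" and then modelling adherence.** That sentence concerns exact fidelity to an individually tailored programme. The weekly questionnaire records how often patients attended and exercised. Both can hold.

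These limits govern how much can be said about the treatment coefficient. They do not rescue the adherence coefficient, which is the quantity the sub-analysis was designed to deliver.

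**Conclusion.** The concern holds in limited form. The planned test cannot establish whether adherence affects pain: association through prognosis, pain or the physiotherapist's discretion would produce the same coefficient. The treatment coefficient from that model should not be interpreted, because it is biased if arm influences adherence together with prognosis, or if pain drives adherence. If adherence is a true mediator, the model also no longer estimates the total effect.

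Size and direction cannot be fixed from the documents. Under assumed shared prognosis, -2.0 became -1.50 to -2.26; where pain drives adherence, the distortion can be larger, cancel or reverse. The intention-to-treat primary result is untouched. This is a correction to a stated secondary method that should be made; it does not threaten the trial's main conclusion.

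**What to change.** In Methods for additional analyses, replace the adherence-adjusted model with two statements.

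1. Adherence (supervised visits and home sessions) will be described by arm, and no treatment effect will be reported from a model containing adherence.
2. If a relation between adherence and pain is of interest, adherence early in the programme (for example PT weeks 1 to 6) will be related to VAS at PT week 12, given earlier weekly VAS, separately within each arm. The result will be labelled exploratory and associational.

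Randomised arm should not be used as an instrument for adherence. Both groups receive the same physiotherapy and arm acts on pain through surgery, so the exclusion restriction fails. Weighting methods would need the assumption of no unmeasured confounding and would not restore the randomised comparison by themselves.

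The cost is a change of wording; the weekly data are already planned. The drawback is precision: each within-arm analysis has at most 20 patients, or about 16 if the anticipated 20% loss occurs.
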